##### Task Accomplishment

Metrics on task accomplishment are designed to show if a patient re-acquired the ability to complete the task irrespective of the underlying control strategy. With regard to standing balance, this is exemplified first by the level of independence following clinical scales and second by (traditional) posturographic measures of body sway that show how well a subject can stabilize their center-of-mass within the base of support. Therefore, these outcome variables will be used to address the process of regaining and optimizing the ability to maintain standing balance.

**Berg Balance Scale - standing unsupported item (BBS-s)**: The BBS-s assesses the ability to maintain assesses the ability to maintain a quiet standing posture without using the arms or support by another person. A score is assigned based on the level of independence needed to complete this task, where a score of 0 indicates no standing ability and a score varying between 1 and 4 indicate independent stance over 30 s to 2 min. The BBS has been reported to have excellent internal consistency as reported by a systematic review (58).**Stance stability**: To investigate overall stability when subjects attempt to stand quietly, we will calculate the root mean square (RMS) velocity of the net COP (i.e., combining two feet together without correction for feet orientation) in AP and ML direction. As the position of the net COP and the vertical representation of the body's center-of-mass correlate (59) these metrics reflect the ability to stand with minimal body sway.

### Data Analysis

#### Descriptive Analysis

Subject's demographics at baseline together with lesion characteristics will be descriptively analyzed. The length of stay in the inpatient rehabilitation facility and discharge destination will be reported. In addition, adherence to the study protocol will be illustrated by reporting the number of subjects leaving the study prematurely and reasons for dropping out entirely or missing assessments. We will use the BBS-s to show how soon subjects recovered standing balance and were able to participate in posturographic assessments.

#### Statistical Analysis

##### Project A

In project A, we aim to investigate time-dependent changes in metrics of quiet stance balance control. To estimate how each parameter is changing as a function of time poststroke, we use a random coefficient analysis (or mixed model analysis) with “time” of measurements as the main fixed effect (JMP Pro, version 15). Additionally, “time” will be entered as an independent covariate in form of an subject-specific slope (i.e., the interaction term “participant^*^time”) to adjust for dependency of repeated observations. However, the greatest advantage of this method is its flexibility in dealing with missing values. The latter may result from subjects being unable to stand at first occasions, being unavailable due to hospital discharge or transfers, or by no longer corresponding to eligibility criteria for example due to a recurrent stroke or other sudden medical condition (potentially) affecting outcome variables. Moreover, the value on the addressed metric at 3 weeks poststroke will be added to account for inter-subjects variability.

In addition, fixed covariates that are hypothesized to be potential confounders will be entered in the model. This includes “gender,” “age” and “BMI” considering their influence on standing balance control. [i.e., females and elderly tend to show greater body sway (60) and obesity is associated with instability (61)]. Second, stroke “side” and “type” will be added, as right-sided lesions typically result in greater balance deficits (62) and subjects with hemorrhagic strokes may display delayed recovery (63). Lastly, “equipment” is added as a potential confounder considering technical variations in measuring instruments.

Statistical analysis of the difference in each measure of quiet stance balance control between subjects and healthy controls will be performed using the Mann-Whitney U test for each measuring system separately.

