### Objectives

In the current manuscript, we describe an observational cohort study that aims to prospectively investigate the time course of recovery of quiet stance balance control in the first 12 weeks after a first-ever hemispheric stroke. The relatively low functional demands of this condition (as compared to perturbed stance or walking) enables us to describe the process of balance skill re-acquisition even in more-severely impaired subjects and in the time window of spontaneous neurological recovery. Simultaneously, we will clinically observe the time course of recovery of lower limb motor impairments to investigate longitudinal associations with this leg's contribution to balance control.

The pre-defined research questions and hypotheses are:

What is the time course of recovery in the first 12 weeks poststroke in terms of balance control (a-)symmetries and overall stability during quiet stance? (i.e., project A).

First, we hypothesize that improvements in balance control symmetries toward values seen in healthy controls, as assessed through bilateral posturography (i.e., between-limb synchronization and contribution measures of corrective COP movements), are restricted to the first 5 weeks poststroke. Second, we hypothesize that an improved ability to maintain a stable standing position following traditional posturographic measures of body sway (i.e., stance stability) may develop beyond the time window and up until 12 weeks poststroke. As such, these later changes are hypothesized to reflect compensatory body stabilization exerted through the less-affected leg.

How are improvements in muscle synergies and ankle strength of the most-affected leg longitudinally associated with this leg's contribution to quiet stance balance control in the first 12 weeks poststroke? (i.e., project B).

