First, we hypothesize that clinical improvements in muscle synergies (i.e., Fugl-Meyer Motor Assessment) and strength (i.e., Motricity Index) at the hemiplegic side are mainly seen within the first 5 weeks poststroke, in accordance with previous longitudinal studies investigating time-dependent change (20, 23). Second, we hypothesize to find within this time window longitudinal associations between recovery on these scales and improved between-limb symmetry in balance control. This means that clinically observed improvements in motor impairments relate over the first weeks to an improved ability of this leg to contribute to corrective COP movements while standing quietly.

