### Design

The current recovery study is a non-interventional observational study meaning that no systematic interventions are applied next to usual care. For the duration of inpatient rehabilitation, this consists of 30- to 60-min sessions of physical and occupational therapy each workday following local guidelines.

After eligible subjects are included within the first 3 weeks poststroke, serial measurements will be scheduled at 3, 5, 8, and 12 weeks poststroke. Clinical evaluations are performed by the same assessor for each participant to decrease the effect of inter-rater variability when measuring within-subject change. In total, two physical therapists are available for clinical testing who underwent a training period to standardize assessment procedures prior to the study start. As soon as subjects are able to stand independently barefoot over at least 30 seconds, bilateral posturography will be performed during a standardized quiet stance task. For this purpose, either two separate force-plates (Type OR 6-7, AMTI, MA, US; measurement frequency 1 kHz) arranged in a side-by-side configuration as part of a stationary movement analysis laboratory (*M*^2^*OCEAN*, University Hospital Antwerp, Edegem, Belgium) or a portable pressure-plate system (0.5 m footscan 3D, RS Scan, Belgium; measurement frequency 500 Hz) will be used. This provides the advantage of executing this study in multiple (clinical) settings to facilitate recruitment and continuous data acquisition. Importantly, repeated within-subject measurements are always performed with the same equipment and these measurements are performed by a trained physiotherapist who is educated in using the measuring instruments.

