##### Quality of Task Performance

Quality of task performance is “defined through a direct comparison of a patient's motor execution of a task […] to able-bodied control subjects” (35). This means that the closer the movement matches those seen in controls, the better the quality. With regard to standing balance, quality of performance is best reflected by measures that establish the (a-)symmetry between the most- and less-affected side considering that healthy balance control is characterized by equal output generated through the legs in the form of corrective COP movements (39, 56, 57). For this purpose, synchronization and contribution measures will be calculated that show how well both limbs act together (32, 39, 56) and are equally involved (31, 57) in maintaining standing balance. As COP in the ML direction is less meaningful for bipedal balance control (56), we focus on the sagittal plane.

**Between-limb synchronization:** Between-limb synchronization is a measure of the temporal structure and similarity between bilateral COP (39, 56). For this purpose, the mean position is subtracted from left and right AP COP trajectories and, next, a cross-correlation at zero-phase leg on a frame-by-frame basis is calculated. This measure therefore shows how well COP displacements are alike, or synchronized.**Dynamic control asymmetry (DCA)**: DCA is a symmetry index of the root mean square (RMS) of the AP COP velocities for each leg separately (31, 57). A score of zero indicates equal contribution of both legs to balance control and positive or negative values indicating a relatively larger involvement of the less- or most-affected leg, respectively. We use the following equation: Symmetry index: 2x (RMS COP AP velocity *less-affected*- RMS COP AP velocity *most-affected*) / (RMS COP AP velocity *less-affected* + RMS COP AP velocity *most-affected*).

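### Project A predicts a break in recovery at week 5, but its stated analysis names no comparison of change before and after week 5

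*Protocol article*

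**What the plan says.** The Objectives section of the protocol article sets out predictions about the shape of recovery:

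- Improvements in balance control symmetry (synchronization and dynamic control asymmetry, DCA) "are restricted to the first 5 weeks poststroke".
- Improvement in stance stability "may develop beyond the time window and up until 12 weeks poststroke". These later gains are to be read as compensation through the less-affected leg.
- For Project B, gains on the Fugl-Meyer (FMA-LE) and Motricity Index (MI-LE) scales "are mainly seen within the first 5 weeks poststroke".

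Under Design, "serial measurements will be scheduled at 3, 5, 8, and 12 weeks poststroke". There is therefore one interval up to week 5 and two after it.

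The analysis under Project A reads: "To estimate how each parameter is changing as a function of time poststroke, we use a random coefficient analysis". The fixed part is the time "of measurements as the main fixed effect (JMP Pro, version 15"). A participant-by-time term is added "to adjust for dependency of repeated observations", together with the week-3 value of the metric and a set of possible confounders. Project B analyses the clinical scales in a similar way and takes P-values from Wald tests of the regression coefficients, two-sided at 0.05.

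The article does not say whether fixed time is continuous or categorical. It names no knot, non-linear term or between-visit contrast. The Mann-Whitney tests compare patients with controls and do not concern change over time.

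**The concern.** The prediction has two parts: change up to week 5, and little or none after it. A single time effect addresses whether the outcome changes at all over weeks 3 to 12. It does not address when. The subject-specific slope does not fill the gap, because it describes how patients differ around the average course and is entered to handle correlation.

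The stake is interpretation. The article reads early symmetry gains as restitution and late stability gains as compensation, so its main conclusion depends on separating the two windows. If the comparison is not named beforehand, the analysts must choose it, and decide what counts as no further change, after seeing the data. The same gap affects the stability prediction and the FMA-LE and MI-LE prediction.

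**Working it through.** The plan has no figure of its own to reproduce here. The sample of 60 rests on recruitment and drop-out rates, not on a power calculation. The check asks what each reading of the time effect would show under two true courses with the same total change D.

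**Inputs.** Visits at 3, 5, 8 and 12 weeks (Design). Plateau course: means 0, D, D, D. Steady course: D(t − 3)/9, that is 0, 2D/9, 5D/9, D.

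**Reading 1: linear time, week 3 as an outcome occasion.**

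- Mean week = (3 + 5 + 8 + 12)/4 = 7; deviations −4, −2, 1, 5.
- Sxx = 16 + 4 + 1 + 25 = 46.
- Plateau: Sxy = (−2 + 1 + 5)D = 4D; slope = 4D/46 = 0.087D per week.
- Fitted change in weeks 3-5: 2 × 0.087D = 0.17D (truth D).
- Fitted change in weeks 5-12: 7 × 0.087D = 0.61D (truth 0).

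For any data, a line gives 2/9 (22%) of its fitted change to weeks 3-5 and 7/9 (78%) to weeks 5-12. The split is fixed by the visit dates.

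**Reading 2: linear time, week 3 only as a covariate.** The outcomes are weeks 5, 8 and 12. The plateau is then D, D, D and the slope is 0. The time effect does reflect change after week 5, but the early change no longer appears in it, so the two windows are still not compared. The text does not settle whether reading 1 or reading 2 applies.

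**Reading 3: categorical time.** The overall 3-df test says only that some visit differs. Coefficients against week 3 are:

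| Coefficient | Plateau | Steady |
|---|---|---|
| Week 5 − week 3 | D | 2D/9 |
| Week 8 − week 3 | D | 5D/9 |
| Week 12 − week 3 | D | D |

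All are non-zero under both courses. The first is the early change. Change after week 5 is the third minus the first, which the same fit can give but which is not named.

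**Illustration with assumed values.** The documents give no SD or effect size. Assume residual SD 1, between-subject SD 1, slope SD 0.05 per week, total change 0.8 and complete data, with n = 60 × 0.85 = 51 (15% drop-out, Sample Size Justification). Power at two-sided 0.05:

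| Test | Plateau | Steady |
|---|---|---|
| Linear slope | 0.89 | 0.98 |
| Overall time, 3 df | 0.99 | 0.94 |
| Week 12 − week 5 | 0.05 | 0.86 |
| Weekly rate before minus after week 5 | 0.93 | 0.05 |

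The first two tests usually reject under either course, so they do not tell the courses apart. The last two do. With total change 0.5 to 1.0 and n = 40 to 60, power of the rate-difference test under the plateau ranges from 0.48 to 0.997.

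**Precision of the late change.** The variance of week 12 minus week 5 per patient is 2 × 1² + 0.05² × 7² = 2.1225. The 95% half-width is 1.96 × √(2.1225/51) = 0.40 residual SD, and 0.37 to 0.45 for n = 60 down to 40. Against an assumed total change of 0.8, a non-significant late change would leave room for a sizeable one.

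**The case against.** Several points on the other side have force.

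- **The coding of time is not stated.** The 0.17D/0.61D split needs linear time with week 3 as an outcome row. A subject-specific slope suggests continuous time but does not fix the coding of the fixed effect. With categorical time the needed contrasts come from the same fit. This stands. A reader might infer that Project A cannot answer its own question; the text does not support that. The data could support the comparison, but the article does not name it.
- **A time effect is not empty.** A reader might infer that it will be significant whether or not the prediction is true. The Discussion reports that DCA showed little tendency to diminish during inpatient rehabilitation in earlier work, so no change at all is a live alternative for that outcome, and a time effect addresses it.
- **The detail may be in an analysis plan that is not shown.** In part this stands: contrast lists are often kept there. But the article states both the prediction and the model, with random effect, covariates, tests and software, and the two do not match.
- **The study is framed as estimation.** The article calls for explorative research and gives no basis for a power analysis. A compulsory equivalence bound would therefore ask too much. Intervals for the two windows serve the stated aim.

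A reader might also infer that synchronization, being a correlation ("a cross-correlation at zero-phase leg on a frame-by-frame basis is calculated"), would flatten near 1 and imitate the plateau. Steady recovery of 0.1 per week on the Fisher-z scale from 0.5 (assumed values) gives r = 0.462, 0.604, 0.762 and 0.885. The rise is 0.604 − 0.462 = 0.142 before week 5 and 0.885 − 0.604 = 0.281 after it. That slows but does not look like recovery ending at week 5, so it is no ground for a change of scale. Nothing in the article supports a log scale for velocity either.

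**Conclusion.** The concern holds as a mismatch between a stated prediction and a stated analysis. The prediction is about change before against change after week 5; the analysis as written names no such comparison, for symmetry, for stability or for the clinical scales.

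The size depends on the reading. With linear time and week 3 as an outcome occasion, a true plateau at week 5 would be reported with most of its fitted change after week 5 (0.61D against 0.17D). With week 3 as covariate only, that distortion disappears but the early change leaves the time effect. With categorical time, nothing is distorted and the late change is merely unnamed. The power figures rest on assumed variances and effect sizes and only illustrate the contrast between tests.

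**What to change.** In the Project A analysis, and by reference for the clinical scales in Project B:

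1. Model fixed time as a four-level factor, or as piecewise linear with a knot at week 5.
2. Keep week 3 as an outcome occasion and do not also enter the week-3 value as a covariate in that model.
3. For each balance outcome, and for FMA-LE and MI-LE, prespecify the week 5 minus week 3 change, the week 12 minus week 5 change, and the difference in weekly rate between the two windows, each with a 95% confidence interval.
4. State that recovery will not be called confined to the first 5 weeks because the late change is non-significant; report the interval for the 5-to-12-week change instead. A formal bound for negligible late change is optional.

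This needs no new visits or data. A factor uses two more degrees of freedom than a line, and a single knot one more. The early estimate will rest on fewer patients, since those who cannot yet stand at week 3 have no posturography then; this limit comes from the design and should be reported alongside the result.

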##### Project B

After describing the recovery time course, we aim to investigate longitudinal associations between motor impairments in terms of leg muscle synergies (i.e., FMA-LE) and ankle strength (i.e., ankle item of the MI-LE) serving as independent variables, and the DCA which is the dependent variable. First, we analyze the pattern of neurological recovery following these clinical scales by using similar methods as outlined above. Second, we will apply a recently discussed hybrid model (64) to investigate longitudinal associations over the first 12 weeks poststroke. This method has the advantage of disentangling the between- and within-subject effects of this relation.

The between-subjects covariate score is determined as the individual average value over time of the independent variables which reveals the association irrespective of the development over time. On the other hand, the within-subject covariate is calculated as the observed value at each time point minus the individual average (i.e., deviation score). By this, we can estimate whether longitudinal changes of the dependent and independent variables within a subject are associated, i.e., are increasing scores on the FMA-LE or MI-LE ankle item related to changes following the DCA. Similar covariates will be entered in the model and tested on significance.

For all statistical tests, the likelihood ratio test will be used to examine the need to enter random effects into the model and the Wald test will be used to obtain *P*-values for regression coefficients in the final model. A 2-tailed significance level of 0.05 will be used for all analyses.

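### Project A enters each metric's 3-week value as a covariate, so patients who cannot yet stand at week 3 fall out of the posturographic models unless an unstated rule handles the missing value

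*Protocol article*

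**What the plan says.** The Design section of the protocol article sets the occasions: "serial measurements will be scheduled at 3, 5, 8, and 12 weeks poststroke". Table 1 marks between-limb synchronization, dynamic control asymmetry (DCA) and stance stability at each of them, so week 3 is the first outcome occasion. The same section makes the measurement conditional: "As soon as subjects are able to stand independently barefoot over at least 30 seconds, bilateral posturography will be performed".

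The Project A paragraph under Statistical Analysis specifies a random coefficient model with time as the main fixed effect and a random term "in form of an subject-specific slope". It says that "the greatest advantage of this method is its flexibility in dealing with missing values", and on the causes of missing values: "The latter may result from subjects being unable to stand at first occasions". It then adds: "Moreover, the value on the addressed metric at 3 weeks poststroke will be added to account for inter-subjects variability".

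The Objectives explain that quiet stance was chosen because it "enables us to describe the process of balance skill re-acquisition even in more-severely impaired subjects". The article does not say whether week-3 rows remain in the outcome once the 3-week value is a covariate, and it gives no rule for patients who lack that value.

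**The concern.** The paragraph chooses a method because it copes with late standers, then adds a term that late standers cannot have. Likelihood estimation uses all observed outcomes, but this does not extend to a missing predictor: by default the row is excluded. The 3-week value is constant within a patient, so every row of a week-3 non-stander is excluded.

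What is lost is these patients' data from weeks 5, 8 and 12. Those recordings bear directly on the second hypothesis, that stance stability keeps improving up to week 12, and they come from the more severely impaired patients whom the study says it wants to describe.

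There is also a structural difficulty. The first hypothesis confines gains in symmetry to the first 5 weeks, and with this schedule only the interval from week 3 to week 5 can show them. Using the start of that interval as a covariate affects how the change is estimated, in one way if the week-3 rows are kept and in another if they are removed.

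**Working it through.** **Plan's own figure.** The article gives neither the share unable to stand at week 3 nor a power calculation. The only related figure is the rule of 10 subjects per variable under Sample Size Justification: 3 to 4 covariates need 30 to 40 patients, against 60 recruited, or 60 × 0.85 = 51 after 15% drop-out.

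**Step 1: patients left.** Let p be the share unable to stand at week 3 (assumed). Patients in the model = 60 × (1 − p), or 51 × (1 − p) if all drop-outs are also removed. The second figure is pessimistic, because a mixed model keeps a drop-out's earlier recordings.

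**Step 2: recordings lost.** If every late stander stands by week 5 and nothing else is missing, 60p × 3 recordings are discarded out of 60 × 4 − 60p available, a share of 3p / (4 − p). This is the most that can be lost for a given p under no other missingness; later recovery of standing lowers it.

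| p | left of 60 | left of 51 | share of recordings discarded |
|---|---|---|---|
| 10% | 54 | 45.9 | 18/234 = 7.7% |
| 20% | 48 | 40.8 | 36/228 = 15.8% |
| 30% | 42 | 35.7 | 54/222 = 24.3% |
| 40% | 36 | 30.6 | 72/216 = 33.3% |
| 50% | 30 | 25.5 | 90/210 = 42.9% |

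The plan's own 10-per-variable rule then supports 5.4 variables at p = 10%, 4.2 at 30% and 3.0 at 50%.

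**Step 3: the week-3 value predicting itself.** A simulation used n = 60, categorical time, and a random intercept and slope. The assumed values were DCA means 0.80, 0.60, 0.55 and 0.55, between-subject SD 0.35, slope SD 0.02 per week and residual SD 0.15. With complete data (120 runs):

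- 3-to-5-week change: −0.201 without the covariate, and −0.201 with it and week-3 rows kept.
- Theoretical SE of that change: √(2 × 0.15² + 0.02² × 2²) / √60 = 0.0279. Model SE: 0.0279 without the covariate and 0.0260 with it; 0.0260 / 0.0279 = 0.93, so about 7% too small.
- Random-intercept variance: 0.118 without the covariate, 0.001 with it.
- The error in the SE is not in one direction. For the 3-to-12-week change the model SE with the covariate was 0.0377 against a theoretical 0.0359, about 5% too large.
- Coefficient of the 3-week value: 0.92 with week-3 rows kept, 0.84 with them removed. In the latter case the model has no 3-to-5-week time term.

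**Step 4: late standers who improve less.** Here 30% could not stand at week 3, 40% of these also had no week-5 value, drop-out was 15%, and late standers were assumed to improve by 0.1 less (40 runs). The mean number of patients in the model was 58.7 without the covariate, 42.8 with it and week-3 rows kept, and 40.6 with them removed. The estimated 3-to-5-week change was −0.181 without the covariate and −0.201 with it. The value built in for week-3 standers was −0.200, and for the whole cohort −0.2 + 0.1 × 0.3 = −0.170.

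**The case against.** Several points on the other side are sound.

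- A reader might infer that the 3-to-5-week change is estimated wrongly as such. The documents do not support that. With complete data and week-3 rows kept, the point estimate among week-3 standers is unaffected. A patient who could not stand at week 3 has no observed 3-to-5-week change under any analysis; without the covariate, such patients inform that contrast only through the model. The whole-cohort value in Step 4 includes week-3 values for people who were not standing, which cannot be measured.
- Bias in the average change requires change to be related to severity. That link was assumed in Step 4; the article does not report it.
- With week-3 rows removed, the change can still be recovered as the adjusted week-5 mean minus the mean 3-week value. It is no longer a direct time contrast, but it is not beyond reach.
- A reader might infer that the covariate replaces a random intercept. The end of the Project B section leaves the need for random effects to a likelihood ratio test, so an intercept is not excluded.
- A reader might infer that Project B has the same defect. Its sentence, "Similar covariates will be entered in the model and tested on significance", most naturally refers to the confounders (age, gender, BMI, stroke type and side, equipment). Where Project B models FMA-LE and MI-LE themselves, the week-3 score does not depend on standing.
- The missing-data advantage is not lost altogether. Gaps after week 3 from discharge, transfer or recurrent stroke are still handled.
- A full analysis plan might contain a rule for the missing covariate.

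These limit the size and reach of the point, but the central conflict remains. The article itself specifies the covariate and itself expects patients without a value for it. A random intercept alone would not bring those patients back while the covariate stays.

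**Conclusion.** The point holds for the Project A posturographic models. Followed as written and fitted in the ordinary way, the plan drops week-3 non-standers with all their later recordings. For these patients that undoes the stated missing-data advantage, and it narrows the time course to early standers. On an assumed 10% to 50% unable to stand at week 3, 54 to 30 of 60 patients remain. The Berg standing item is not affected, since it is planned as a descriptive measure and can be scored in non-standers.

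The effect on the estimates is more modest. If week-3 rows are kept, the intercept variance collapses and the SE of the 3-to-5-week change is somewhat too small (about 7% under the simulated variances). If they are removed, that change is no longer a direct contrast. Bias in the average change depends on a link between change and severity; without one, the cost is lost data. The sizes rest on the assumed share, the assumed variances and the default deletion of rows with a missing covariate. This should be fixed before the models are run, but it does not call the design or the data into question.

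**What to change.** In the Project A posturographic models, delete the 3-week outcome value as a covariate and keep week 3 as an outcome occasion. Include a random intercept together with the random slope, so that the intercept carries the between-subject variability the covariate was meant to absorb.

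If adjustment for initial severity is wanted, use week-3 FMA-LE or MI-LE. Table 1 schedules both at week 3, and neither depends on meeting the 30-second standing condition.

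State what the covariate sentence in Project B covers. If it is meant to include the 3-week DCA, remove it there too.

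The cost is about a sentence of analysis wording in each place. No new data are needed, and recordings already planned for late standers are retained.
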